### Participant follow-up

5.8.

Clients will be followed up to determine subsequent hospitalisation, major medical events, and interventions at 6 and 12 months. Similar ICD codes for acute CHF will be used for screening information. Data extraction will include a combination of case notes review, medical databases, and contact with PHC and clients directly. Participants requesting changes in answers provided will be discussed at this or any interval to raise this point.

### End points

5.9.

The study endpoints for each phase are: Phase 1 – documentation of health journeys of patients; Phase 2 – interrogation of CFPI and SCRinHF tools for self-management capabilities and readmission risks; and Phase 3 – all data will be accumulated and discussed in the Delphi process. The primary endpoint is the readmission risk as scored by CFPI and SCRinHF and the correlation between the two tools. In addition, the following data will be collected: detailed maps of individual patient journeys and a patient and staff questionnaire on the process. Validation and times to complete the short and long forms will be recorded. The primary endpoint is 80% concordance in MACE and medical events between CFPI and SCRinHF tools. Secondary endpoints are data for cost analysis, and to inform the focus group in planning an RCT for efficacy, validity, reliability, and variability.

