**Methods and analysis:**

*SELFMAN-HF* is a prospective, observational study to evaluate the feasibility and validity of the *SCRinHF* tool, a one-page self-management and readmission risk prediction tool for CHF, with an established, comprehensive CDSM tool. Eligible patients will have CHF with left ventricular ejection fraction <40% and commenced sodium glucose co-transporter-2 inhibitors (SGLT2-i) within 6 months of recruitment. The primary endpoint is the 80% concordance in readmission risk predicted by the *SCRinHF* tool. The study will recruit >40 patients and is expected to last 18 months.

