### Aim and scientific hypotheses

2.1.

The *Self-management in Heart Failure Study* assesses the feasibility and validity of a short form *SCRinHF* tool (6), with the established comprehensive *Flinders Program of Chronic Disease Self-management* (Flinders Program or CFPI) (18–21) for participants who were prescribed an SGLT-2 Inhibitor for CHF. In this, we hypothesise: first, guideline level of care as established by Ref. (1, 2, 12–17), and CDSM can be used to enhance the delivery and uptake of guideline-based care (22–26); second, to achieve this, we have to define clinical pathways. In this study, the model of care is based on patients utilising community cardiologists with community-based triage (Figure 1); third, a short form CDSM tool (*SCRinHF*) will improve efficiency in delivering CDSM programmes without compromising clinical outcomes as compared to the CFPI (Figure 2). The *SELFMAN-HF* study thus aims:

To examine the relationship between CDSM and CHF-related health outcomes over a 12-month period. The CDSM tools that will be used are the CFPI and SCRinHF (Table 1). The study will establish the feasibility of use and the concurrent and predictive validity of the SCRinHF when compared to the CFPI in predicting self-management, clinical measures, and predictive measures of health outcomes (hospital readmissions) in CHF and their limitations and strength

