**Figure 2 fig2:**
[figure not shown]
Summary of standardisation structures for evidence and clinical services. **(A)** Heart failure structures for clinical standards, taxonomy domains to build systems, research methodologies to gain evidence that eventually lead to guidelines. The subsequent steps are observations on: Phase 4 translation to trial type populations, cost-effectiveness to the general population; Phase 5 is a newly coined term to explore logistics in service delivery; the final point are unknowns such as vulnerable populations, new findings that require a bench to bedside approach of gathering evidence and testing these hypotheses in a Phase 3 randomised trial. Population level. RCT – randomised controlled trial [adapted from references (1, 2, 12–16)]. **(B)** Chronic disease self-management is standardised around the Flinders Program of Chronic Disease Condition Management (CFPI). Partners in Health (PIH) are 12 self-rated questionnaire patient complete to assess self-management knowledge, attitudes, behaviours, and impacts of their chronic condition; Cue and Response Interview (C&R) is administered by health workers using an open-ended dialogue on the same questions as the PIH, and rated from the health workers perspective, and shared with the patient; Problem and Goals assessment (P&G) is health worker tool utilising behavioural psychotherapy, open-ended questions negotiate patient-identified problems and formulate goals to address them; care plan records and scores behavioural changes, monitors and progressively implements at patients pace. Barriers, strengths, and priorities identified through PIH, C&R, and P&G are incorporated into fully negotiated care plans [adapted from reference (11)]; the SCRinHF tool extracts and focuses on five domains from the CFPI. As it is a screening tool, domains tested can be re-explored should a patient be identified as at high risk and require more intensive support.

**Table 1 tab1:** SCRinHF heart failure readmission risk scoring tool.

Domains of care	Heart failure ambulatory readmission risk dimensions of care	#Yes	No	*D
1. Baseline readmission risk	Comorbid risk [Ref (1–3)]	1–3+	0	
	Managing ADL	1	0	
	Adequate Social supports	1	0	
	Compliance	1	0	
	Mood – neurovegetative, psychological [Ref (4)]	1	0	
2. Living at home (skills & goals) Self-care maintenance Self-care management Self-care confidence/efficacy	a. Do you know “how to (skill).to achieve (goal)”… [Ref (5, 6)]			

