### Assessment of study data, measures, recommendations, and intervention (Phase 2)

5.3.

Details of the CFPI, heart foundation cardiovascular chronic disease tools, and patient assessment and chronic illness care satisfaction questionnaire (PACIC) are previously summarised [Table 3 in Iyngkaran et al. (3)] and published (3, 7, 8, 11). The CFPI tool and PACIC will be used to obtain information on patients’ CDSM capacity and patient satisfaction informing the CHF journey over 12 months. The PACIC is in three parts, where self-management assumes a component of the third category. Other study measures include the assessment of participants’ clinical changes in CHF and general wellbeing through the 6-month CFPI score, NYHA class, MLWF and 6MWT, and plasma NT-proBNP (Figure 3). Data on readmissions and mortality will be obtained from patient interviews and, if possible, healthcare records from main health providers, hospitals, primary healthcare (PHC) records, and community cardiac services. Cost–benefit analysis will be determined using standard billing criteria for public hospital funding Medicare Australia. These data will be compared with any ongoing prospective works on the CHF patient journey in Victoria. All enrolled patients will receive routine medical care as per Heart Foundation guidelines 2018 (27, 28). No additional investigations will be required from usual care. Comparing the long form CFPI and short form (*SCRinHF* tool) – trained staff who administer the CFPI will record the time to complete the process. The *SCRinHF* tool (Table 1) will be completed by an independent staff from those who filled in the CFPI. They are blinded to patients and will receive access to raw data on patients. The time to complete this will also be recorded.

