### Expected outcomes

5.12.

The primary outcomes are to achieve concordance in readmission risk between CFPI and SCRinHF, and the number of patient readmissions to the hospital. The secondary outcome is to achieve convergent validity between CFPI and SCRinHF and potential economic cost benefits using the SCRinHF tool.

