A strength of this study is the ability of the observational sample size to inform a future randomised study, by the event rates anticipated with the CHF inclusion criteria (LVEF <40%). In Australia, an SGLT-2i can be provided to all patients with NYHA class II and LVEF <40%; thus, its use requires a standardised baseline, and it requires education on self-management to use it safely. In addition, we were also able to leverage on previous works which established performance measures (5, 12, 13, 15, 16, 29) some updated (14), to inform and extract parameters for this study.

An important limitation in study-specific tools is questionnaires that have qualitative and quantitative components [Tables 2, 3 previously published (3)]. The frameworks for CDSM and CPFI (11) have been previously detailed. These goals (11, 19–21) and established CHF readmission risk scores were foundations on which the SCRinHF tool was modelled. The limitations of traditional tools, including patient fatigue (45–60 min to complete), were the impetus for the development of a one-page tool; overlaps in questions between tools and investigators were the motivation to train end users to populate other tools with overlapping questions where appropriate [previously published Table 2 Iyngkaran et al. (3)]. Monitoring clinical changes with CHF is also important. The balance between quick and less accurate assessments such as NYHA classification, general chronic disease scores, and CHF-specific scores can impact clinical standardisation and require thoughtful considerations (30–34). These points will also be factored in when informing a larger definitive RCT.

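### The primary endpoint compares SCRinHF with a CFPI readmission risk that the article never defines, and agreement between the two tools would not show that either one predicts readmission

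*Protocol article*

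**What the plan says.** Section 5.9 (End points) defines the primary endpoint twice. The first sentence reads "The primary endpoint is the readmission risk as scored by CFPI and SCRinHF and the correlation between the two tools". The second reads "The primary endpoint is 80% concordance in MACE and medical events between CFPI and SCRinHF tools". The abstract has "The primary endpoint is the 80% concordance in readmission risk predicted by the" SCRinHF tool, and Section 5.12 (Expected outcomes) has "The primary outcomes are to achieve concordance in readmission risk between CFPI and SCRinHF, and the number of patient readmissions to the hospital".

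On what the CFPI measures, the Figure 2 legend says that its patient questionnaire (PIH) serves to "assess self-management knowledge, attitudes, behaviours, and impacts of their chronic condition". The Cue and Response interview covers the same questions from the health worker's side. The other two parts deal with patient-identified problems and goals, and with a care plan that scores change in behaviour. Section 5.3 says that the CFPI, with the PACIC, "will be used to obtain information on patients’ CDSM capacity and patient satisfaction".

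SCRinHF is different. Table 1 is titled as a readmission risk scoring tool and has low, moderate and high readmission tiers. The Discussion adds that, besides the self-management goals, "established CHF readmission risk scores were foundations on which the SCRinHF tool was modelled".

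The aim in Section 2.1 is to establish "the concurrent and predictive validity of the SCRinHF when compared to the CFPI in predicting self-management, clinical measures, and predictive measures of health outcomes", with hospital readmissions named as the health outcome. Section 3 calls the CFPI the gold standard and lists prediction of 12-month cardiovascular outcomes, including readmission. Section 5.8 collects hospitalisations and major events at 6 and 12 months.

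**The concern.** A concordance endpoint needs the same quantity from both instruments. Here SCRinHF yields a readmission tier, while the CFPI, as this article presents it, yields ratings of self-management. How a CFPI result becomes a readmission risk is not stated.

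The second difficulty would remain even if that rule were written down. Agreement between two tools says nothing about whether either is right about readmission. SCRinHF also scores items such as comorbidity, daily living, social support, mood and acuity of presentation. Where these drive its tier, disagreement with a self-management rating may be correct, yet it would count against the tool. The study is meant to inform a randomised trial, so a primary result read as evidence of readmission prediction would carry forward into that design.

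**Working it through.** No sample size or power figure in the article depends on this point, and 80% is a target rather than a calculated result. There is therefore no plan figure to reproduce. The check is a comparison of the texts, followed by short arithmetic.

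**1. What each tool delivers, as described.**
- SCRinHF (Table 1): a score and three readmission tiers.
- CFPI (Figure 2 legend, Section 5.3): self-rated and worker-rated self-management, problems and goals, a care plan scoring behaviour change; its stated use is self-management capacity. No readmission score, band, cut-point or mapping appears anywhere in the article.

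**2. Which endpoint statements need a CFPI readmission risk.**
- Section 5.9, first sentence: yes, explicitly.
- Section 5.12: yes, for its concordance part.
- Section 5.9, second sentence: unclear. It is worded as agreement between tools but refers to events.
- Abstract: names only SCRinHF and does not say what it is concordant with.

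**3. Agreement does not imply prediction.** Illustration with 40 patients (the minimum in Section 4), assuming 20 are readmitted.
- Both tools flag the same 10 patients; 5 of the 10 flagged and 15 of the 30 unflagged are readmitted. Agreement = 40/40 = 100%. Sensitivity = 5/20 = 25%. Specificity = 15/20 = 75%. Sensitivity + specificity − 1 = 0, so neither tool predicts anything.
- SCRinHF flags exactly the 20 readmitted patients; the CFPI band flags 10 of them and nobody else. Agreement = (10 + 20)/40 = 75%. A perfect predictor misses the 80% target.
- Two unrelated tools that each flag 10% agree by chance in 0.10² + 0.90² = 82% of patients.

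**4. Precision.** For an observed 32/40 = 80%, the exact (Clopper–Pearson) 95% interval is 64% to 91%.

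**5. How far an unstated CFPI cut matters.** Assume bivariate normal scores with correlation ρ, SCRinHF flagging a fixed fraction s and the CFPI flagging a fraction q. Agreement = 1 − s − q + 2·P(both high). Table 1 sets the SCRinHF tiers, so s is held fixed and only q moves.
- ρ = 0.5: the best agreement over all q is 77% at s = 25%, 71% at s = one third, 68% at s = 40% and 67% at s = 50%. It reaches 80% only if s is about 20% or less.
- ρ = 0.7, s = 40%: 61% to 76% for q between 10% and 75%.
- ρ = 0.9, s = 40%: 70%, 82%, 86%, 84% and 65% for q = 10%, 25%, 40%, 50% and 75%.

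This reduces three tiers to two, and both ρ and s are assumptions.

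**The case against.** The strongest reply has four parts.

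*The rule may exist elsewhere.* This is a condensed article that refers to earlier publications for CFPI details. A reader might infer that the CFPI can never serve as a readmission reference, or that staff would have to construct a band after seeing the data. Neither is supported: the instrument itself is not shown, a prespecified mapping is possible, and nothing says that a mapping would be made late. What stands is that this article fixes its primary endpoint on a quantity that its own account of the comparator does not supply. The appendix it mentions is cited for the SCRinHF manual, not for a CFPI risk score.

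*Prediction is already an aim.* Sections 2.1 and 3 say so, Section 5.12 counts readmissions as a primary outcome and Section 5.8 collects the events. It would therefore be wrong to say that the study ignores observed outcomes. But a count of readmissions is not an assessment of either tool, and no endpoint statement clearly links classification to each patient's events. The second sentence of Section 5.9 can be read as anchored to events, so the defect does not attach equally to every wording.

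*The cut-point argument is limited.* A reader might infer that the choice of CFPI cut alone decides whether 80% is met. With SCRinHF held fixed that is not generally so. At correlation 0.5 the target is out of reach at every cut unless SCRinHF flags about 20% or fewer. The cut decides the result only in some settings, such as the 0.9 example.

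*The design is legitimate for its stage.* Comparing a short form with its long form is a recognised concurrent-validity design, SCRinHF draws five domains from the CFPI, and the study is described as a hypothesis-generating feasibility study. That supports keeping the comparison, under the right name.

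**Conclusion.** The concern holds for the CFPI as this article describes it. The comparison in the first endpoint sentence of Section 5.9 and in Section 5.12 lacks a defined readmission risk on the CFPI side. Whatever rule might supply one, agreement between the tools would show concurrent validity only and could not carry the claim of predictive validity in Sections 2.1 and 3.

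The consequence is one of interpretation: 100% agreement is compatible with zero predictive value, and a perfect predictor can score 75%. Those two examples rest on an assumed 20 readmitted patients out of 40, but the logic does not depend on that number. No claim is made that the 80% target would be met or missed.

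**What to change.** Reword the primary endpoint so that each claim has its own reference.

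- **Predictive validity:** compare the SCRinHF band, and separately the baseline CFPI score, with each patient's observed hospitalisation by 12 months. Report sensitivity, specificity and discrimination with confidence intervals for each tool.
- **Concurrent validity:** compare the SCRinHF self-care domains (2 and 3 in Table 1) with the CFPI self-management ratings.
- Remove the CFPI-scored readmission risk as the reference. If a CFPI readmission band is retained, prespecify the rule that produces it.
- Use the same wording in the abstract and in Sections 5.9 and 5.12.

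The cost is a change of wording and a small amount of analysis, since CFPI scores, SCRinHF scores and 12-month hospitalisations are already collected. The price is imprecision. Sensitivity and specificity each rest on only part of about 40 patients: with 20 readmitted, an observed sensitivity of 16/20 = 80% would have an exact 95% interval of 56% to 94%. Section 5.15 expects more than 100 admissions, or over 2.5 per patient if 40 are enrolled (100/40), so patients without an admission may be few and specificity the weaker estimate. The results should be presented as estimates for planning the later trial.

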## Study objectives

3.

The *SELFMAN-HF tests the feasibility and validity of the SCRinHF tool,* comparing the novel one-page tool to the gold standard Flinders Program of Chronic Condition Self-management Tool (CFPI). Feasibility: there are no prior comparisons of short and long form CDSM tools applied to CHF. Validity: first, this will explore comparisons of the SCRinHF to the CFPI in a range of measures including, self-management, clinical progress, and predicting 12 months major cardiovascular outcomes including readmission; and second, the Delphi method to attain peer acceptability and expert consensus on the *SCRinHF* tool.

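### Section 5.9 puts the correlation between CFPI and SCRinHF into the primary endpoint, but a correlation cannot show that the two tools assign the same readmission-risk level; the 80% concordance stated alongside it could, once defined

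*Protocol article*

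**What the plan says.** Section 5.9 (End points) states the primary endpoint twice:

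- First: "The primary endpoint is the readmission risk as scored by CFPI and SCRinHF and the correlation between the two tools". No coefficient is named and no threshold is given.
- A few sentences later: "The primary endpoint is 80% concordance in MACE and medical events between CFPI and SCRinHF tools".

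The abstract (Methods and analysis) has "The primary endpoint is the 80% concordance in readmission risk predicted by the" SCRinHF tool. Section 5.12 (Expected outcomes) has "The primary outcomes are to achieve concordance in readmission risk between CFPI and SCRinHF, and the number of patient readmissions to the hospital", and then "The secondary outcome is to achieve convergent validity between CFPI and SCRinHF and potential economic cost benefits using the SCRinHF tool".

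Section 3 describes the study as "comparing the novel one-page tool to the gold standard Flinders Program of Chronic Condition Self-management Tool (CFPI"). Table 1 turns the SCRinHF result into low, moderate or high readmission risk and attaches a level of support to each. Section 5.15 names descriptive statistics, linear mixed models and generalised estimating equations, but no agreement statistic.

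**The concern.** A short form judged against a reference tool, with an output in risk bands that guide support, is useful to the extent that it puts the same patient at the same level. Correlation answers a different question. Pearson's coefficient measures linear association and a rank coefficient measures ordering, and both ignore a constant difference between the tools. A SCRinHF that reads consistently low against the CFPI could therefore show a high correlation while moving high-risk patients into lower bands.

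If the correlation became the headline result, it could be read as support for substituting the short form, and it would feed into the planning of the future RCT that section 5.9 mentions. Section 5.12 already has a natural place for correlation, the secondary convergent-validity outcome.

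**Working it through.** **Is there a figure to reproduce?** The only numeric target for the tool comparison is the 80% concordance. The article gives it no derivation, so there is nothing to reproduce. The checks below use constructed inputs and are illustrations, not predictions for this cohort.

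**1. Invariance.** Let X be the CFPI score and Y = X − d the SCRinHF score, with d constant. Then Cov(X, Y) = Var(X) and SD(Y) = SD(X), so Pearson r = Var(X) / [SD(X) × SD(X)] = 1 for any d. The ranks are unchanged, so the rank correlation is also 1. Lin's concordance coefficient, which does penalise a shift, is 2 Var(X) / [2 Var(X) + d²]. With d = 1 SD this is 2 / (2 + 1) = 0.67.

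**2. Three bands, 40 patients.** The minimum of 40 is from section 4; the mix is assumed. Suppose the CFPI gives 10 low, 15 moderate and 15 high, and SCRinHF rates every moderate and every high patient one band lower.

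| CFPI | SCRinHF low | SCRinHF moderate | SCRinHF high |
|---|---|---|---|
| Low | 10 | 0 | 0 |
| Moderate | 15 | 0 | 0 |
| High | 0 | 15 | 0 |

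- Observed agreement: 10/40 = 25%.
- Agreement expected by chance: (10/40)(25/40) + (15/40)(15/40) + (15/40)(0/40) = 0.156 + 0.141 + 0 = 0.297.
- Unweighted kappa: (0.25 − 0.297) / (1 − 0.297) = −0.07.
- Mean band difference: −30/40 = −0.75.
- Pearson r = 0.87; rank correlation = 0.89.

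The correlation looks strong although no CFPI-high patient is called high.

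**3. Imperfect correlation plus a shift.** Assume bivariate-normal scores, with both tools cut at the tertiles of the CFPI distribution and SCRinHF shifted down by d. Band agreement is the sum of the three diagonal cell probabilities.

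| Correlation | Shift d | Band agreement | CFPI-high also called high | Linear-weighted kappa |
|---|---|---|---|---|
| 0.8 | 0 | 65% | 72% | 0.58 |
| 0.8 | 0.5 SD | 58% | 45% | 0.48 |
| 0.8 | 1 SD | 46% | 22% | 0.29 |

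At a correlation of 0.9 the band agreement is 74%, 63% and 45%. So even 0.9 with no shift falls short of 80% band agreement under these assumptions.

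**4. Precision at n = 40.** For r = 0.8, Fisher's z gives atanh(0.8) ± 1.96/√37, which back-transforms to 0.65 to 0.89. That interval is the same for all three shifts. For an observed agreement of 32/40 = 80%, the exact 95% CI is 64% to 91%.

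**The case against.** The strongest reply is that agreement is already primary. The abstract and 5.9 each state 80% concordance, and 5.12 states concordance in readmission risk, while correlation appears once as an endpoint and without a threshold. Read as band agreement, the 80% criterion would expose the pattern in step 2 (25% against 80%). This stands, and it limits the point to the correlation component. It is an imperfect safeguard, though: concordance is undefined, 5.9 attaches it to MACE and medical events, and 5.15 names no agreement statistic. Nothing in the text stops a coefficient of 0.80 from being presented as 80% concordance.

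A second reply is that the same sentence in 5.9 also includes the risk scored by each tool, so a shift might be seen in the reported scores. That is possible, but only if the two are on a comparable scale, and the article gives bands for SCRinHF alone.

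A third is that section 2.1 aims at concurrent and predictive validity, for which correlation with a reference tool is commonly used. That is a reason to keep correlation for convergent validity, not to make it primary. The hypothesis in 2.1 that the short form works "without compromising clinical outcomes as compared to the CFPI" is about programme delivery, so it is not used as support here.

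A reader might infer more than the article supports:

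- *That no version of the primary endpoint could detect under-rating.* The concordance statements rule this out.
- *That SCRinHF does read low, or could do so in every patient.* Nothing in the article suggests a shift. On three bands, a patient already rated low cannot go lower; uniform under-rating is possible only on the score.
- *That narrow entry criteria distort the correlation.* LVEF below 40% and a recent SGLT2-i start do not directly restrict what SCRinHF scores, such as social support, mood and self-care skills. Kappa depends on the case mix as well.

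**Conclusion.** The point holds for the correlation component of the primary endpoint in 5.9. No usual correlation coefficient responds to a constant difference, so this component cannot show that SCRinHF assigns the same readmission-risk level as the CFPI. That result is algebraic and needs no assumption about the data.

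The size is illustrative. Under normal scores, tertile bands and shifts of 0 to 1 SD, a correlation of 0.8 goes with band agreement anywhere from 65% down to 46%. The true shift, the true correlation and the band proportions are unknown.

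The study is described as feasibility-stage and hypothesis-generating, so this does not undermine it. It should still be settled before analysis, because the article leaves open which statistic will carry the conclusion.

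**What to change.** 1. In 5.9, remove the correlation from the primary endpoint. Keep the article's own 80% concordance in readmission risk, defined as the percentage of patients placed in the same risk band by both tools, with a 95% CI. Use the same wording in the abstract, 5.9 and 5.12.
2. Report with it the band-by-band cross-table, a weighted kappa with 95% CI, and the mean band difference, so that the direction of any disagreement is visible.
3. State before the data are examined how the CFPI assessment is converted to a low, moderate or high band. The article gives bands for SCRinHF only, and none of the agreement measures can be computed without this rule.
4. Report correlation only under the secondary convergent-validity outcome in 5.12, and name the coefficient.

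Cost: no additional patient data are foreseen, but this is more than a wording change, because the study team must write and justify the CFPI banding rule. The agreement figure may look less favourable than a correlation, and with about 40 patients its interval will be wide (64% to 91% at an observed 80%).

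### The primary endpoint is stated inconsistently in the Abstract, section 5.9 and section 5.12, so the study's conclusion could depend on which version is reported

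*Protocol article*

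**What the plan says.** Four statements in the current text name the primary endpoint or outcome.

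- Abstract, Methods and analysis: "The primary endpoint is the 80% concordance in readmission risk predicted by the" SCRinHF tool. The sentence names no comparator; the CFPI has to be inferred from the context.
- Section 5.9, first statement: "The primary endpoint is the readmission risk as scored by CFPI and SCRinHF and the correlation between the two tools". No threshold is attached.
- Section 5.9, second statement, in the same paragraph: "The primary endpoint is 80% concordance in MACE and medical events between CFPI and SCRinHF tools".
- Section 5.12: "The primary outcomes are to achieve concordance in readmission risk between CFPI and SCRinHF, and the number of patient readmissions to the hospital". No threshold is attached here either.

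Two design features matter for reading these. Under section 5.3 the SCRinHF "will be completed by an independent staff from those who filled in the CFPI", working from raw data on the same patients. Under section 5.8, "Clients will be followed up to determine subsequent hospitalisation, major medical events, and interventions at 6 and 12 months".

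**The concern.** A primary endpoint should identify one variable, one summary statistic and, if a target is set, one threshold. Here all three change from place to place, and section 5.9 does so within a single paragraph. Nothing in the article ranks or reconciles the statements.

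At stake is what the study will be able to say. Its purpose is to test the short tool against one it calls the gold standard, and to inform a later randomised trial. If the versions disagree once the data are in, the report could rest on whichever was chosen, and a reader could not tell from the article which one was meant to decide.

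**Working it through.** The 80% target comes with no derivation, null value or formula, so there is no stated figure to reproduce. The check is mainly textual.

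**Step 1. The statements side by side.**

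| Place | Variable | Statistic | Threshold |
|---|---|---|---|
| Abstract | predicted readmission risk | concordance | 80% |
| 5.9, first | readmission risk by both tools | correlation | none |
| 5.9, second | MACE and medical events | concordance | 80% |
| 5.12 | readmission risk; number of readmissions | concordance; count | none |

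**Step 2. What can be merged.** The Abstract and the first half of 5.12 share one construct, concordance in readmission risk, and differ only in whether 80% is stated. The first sentence of 5.9 concerns readmission risk too, but uses another statistic. Three conflicts remain:

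1. correlation versus 80% concordance;
2. readmission risk versus MACE and medical events;
3. the readmission count, which is a property of the cohort and not a comparison of tools.

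**Step 3. Are correlation and concordance interchangeable?** Take 40 patients (the minimum in section 4), score low, moderate and high as 0, 1 and 2, and use two invented tables.

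- Table A: 20 patients are low on CFPI and moderate on SCRinHF; 20 are moderate on CFPI and high on SCRinHF. SCRinHF is always one class higher, so the correlation is 1.00. Concordance is 0/40 = 0%.
- Table B: 32 are high on both tools, 4 low/high and 4 high/low. Concordance is 32/40 = 80%. Each tool rates 36/40 = 0.90 as high, so the correlation is (0.80 − 0.90 × 0.90) / (0.90 × 0.10) = −0.01/0.09 = −0.11. Chance agreement is 0.90² + 0.10² = 0.82, so Cohen's kappa is (0.80 − 0.82)/(1 − 0.82) = −0.11.

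Both tables are deliberately extreme. They show that the two statistics measure different things, and do not forecast this study's data.

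**Step 4. The MACE sentence.** Both tools are applied to each patient, and each patient's events are observed once. Read literally, the events under CFPI and the events under SCRinHF are the same events, so concordance is 100% by construction or has no meaning. The workable reading is agreement in predicted events, which section 3 supports by listing "predicting 12 months major cardiovascular outcomes including readmission" among the comparisons. Table 1, however, classes patients by low, moderate or high readmission risk. It has no MACE class.

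**Step 5. Precision of an 80% result.** If 32 of 40 patients agree, the exact (Clopper-Pearson) 95% interval runs from the 2.5% quantile of Beta(32, 9) to the 97.5% quantile of Beta(33, 8), that is 64% to 91%. Whichever concordance is kept, the point estimate alone would say little at this size.

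**The case against.** The strongest reply is that this is a condensed article about a feasibility cohort that describes itself as hypothesis generating, with no confirmatory test attached to the 80%. Three of the four statements concern readmission risk by the two tools, and sections 2.1 and 3 give the MACE sentence a sensible meaning as predictive validity.

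Much of this stands. It is too strong to say that there are four mutually incompatible endpoints, or that the MACE version can never be computed. But condensing a protocol explains omitted detail, not conflicting statements, two of them in one paragraph. A feasibility study that sets a numerical target still has to say what the target applies to.

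A reader might infer several further things that the document does not support:

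- *That a CFPI cut-point could be tuned to reach 80%.* The article gives no CFPI readmission-risk category, but it refers tool details to earlier publications, and a cut-point may sit in the unseen full protocol.
- *That 5.12 contradicts 5.9 on convergent validity.* Section 5.12 says "The secondary outcome is to achieve convergent validity between CFPI and SCRinHF". That may concern self-management scores, which section 2.1 also compares, and not the readmission-risk correlation.
- *That the study would succeed on correlation and fail on concordance.* The correlation version has no success threshold. Simulated three-class agreement at a latent correlation of 0.90 is 74–77% for some category margins (33/33/33, 20/20/60, 15/35/50) but 82–86% for others (10/20/70, 10/10/80). The article gives neither a correlation nor margins, so such figures do not size the problem.

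**Conclusion.** The concern holds as an inconsistency in the current text. The primary result is indeterminate as written, because statistic, variable and threshold differ between the Abstract, 5.9 and 5.12, and three of the differences cannot be reconciled by reading the statements together. In 5.9 the 80% target is attached only to the MACE sentence, which is the one that does not compare the tools when taken literally.

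The size is qualitative: the conclusion could depend on the version reported, but nothing in the article allows the likelihood of that to be estimated. The verdict rests on the wording and on two stated design facts (both tools on the same patients, one event history per patient). It does not depend on any sample-size figure or on whether a CFPI cut-point exists elsewhere. A single definition in the unseen full protocol would lessen the practical risk, but would not remove the contradiction in the article.

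**What to change.** State one primary endpoint in the same words in the Abstract, 5.9 and 5.12: agreement between the SCRinHF and CFPI readmission-risk categories, judged against the 80% target and reported with a confidence interval. Specify the CFPI categories, or point to where they are specified, and confirm that they were fixed without reference to the outcome data. That condition matters because section 5.14 schedules an outcome census for December 2022, before the article's publication in May 2023.

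Remove concordance in MACE and medical events as a primary. Replace it with a secondary predictive-validity analysis of each tool's baseline score against observed 12-month events in the same patients. Paired AUCs are one suitable choice. Make the between-tool correlation and the number of readmissions secondary.

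The cost is rewording in three places. If the CFPI categories are not already defined, someone without sight of the outcomes must also define them. No new data are needed, since the scores and 12-month events are already to be collected.
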